# Protocols of a diagnostic study and a randomized controlled non-inferiority trial comparing televisits vs standard in-person outpatient visits for narcolepsy diagnosis and care: TElemedicine for NARcolepsy (TENAR**)**

**DOI:** 10.1186/s12883-020-01762-9

**Published:** 2020-05-11

**Keywords:** Telemedicine, Televisit, Diagnosis, Management, Care, Sleep disorders, Narcolepsy, Sleepiness, Quality of life

## Abstract

**Background:**

Narcolepsy is a rare chronic sleep disorder that typically begins in youth. Excessive daytime sleepiness is the main disabling symptom, but the disease is often associated with severe endocrine-metabolic and psychosocial issues, worsened by a long diagnostic delay, requiring a multidisciplinary approach. The scarcity of reference Sleep Centres forces the patient and family to travel for seeking medical consultations, increasing the economic and psychosocial burden of the disease. Growing evidence suggests that Telemedicine may facilitate patient access to sleep consultations and its non-inferiority in terms of patient satisfaction, adherence to treatment, and symptom improvement for sleep disorders. However, Telemedicine clinical and economic benefits for patients with narcolepsy are still unknown.

**Methods:**

TENAR is a two-part project, including: 1. a cross-sectional study (involving 250 children and adults with suspected narcolepsy) evaluating the accuracy of Teletriage (i.e., a synchronous live interactive sleep assessment through a Televisit) for narcolepsy diagnosis compared to the reference standard; and 2. a two-arm, parallel, open randomized controlled trial (RCT) to demonstrate the non-inferiority of the multidisciplinary care of narcolepsy through Televisits versus standard care. In this RCT, 202 adolescents (> 14 y.o.) and adults with narcolepsy will be randomly allocated (1:1 ratio) either to Televisits via videoconference or to standard in-person outpatient follow-up visits (control arm). The primary outcome is sleepiness control (according to the Epworth Sleepiness Scale). Secondary outcomes are other symptoms control, compliance with treatment, metabolic control, quality of life, feasibility, patient and family satisfaction with care, safety, and disease-related costs. At baseline and at 12 months, patients will undergo neurologic, metabolic, and psychosocial assessments and we will measure primary and secondary outcomes. Primary outcomes will be also measured at 6 months (remotely or in person, according to the arm).

**Discussion:**

TENAR project will assess, for the first time, the feasibility, accuracy, efficacy and safety of Telemedicine procedures applied to the diagnosis and the multidisciplinary care of children and adults with narcolepsy. The study may be a model for the remote management of other rare disorders, offering care access for patients living in areas lacking medical centres with specific expertise.

**Trial registration:**

Number of the Tele-multidisciplinary care study NCT04316286. Registered 20 March 2020.

## Background

Narcolepsy is a rare chronic disorder of hypersomnolence [1] with excessive daytime sleepiness (EDS) as the main disabling symptom. The estimated prevalence in the general population is of 0.02–0.067% [2]. Narcolepsy onset occurs between childhood and young adulthood [3]. However, patients often experience an extended diagnostic delay (14 years in Europe) [4] that may be associated with misdiagnosis and inappropriate resource utilization, increasing the psycho-social impact of the disease [3, 5]. Quality of life and social activities are profoundly impaired in both adults and children [6, 7], and patients need frequent and timely counselling to adjust behavioural and pharmacological treatments. High direct and indirect disease-related costs are reported [8–10]. Metabolic (obesity, diabetes, precocious puberty) and psychiatric comorbidities (mood, anxiety, and eating disorders) are additional common features in narcolepsy [11], and require a multidisciplinary approach. To our knowledge, the ‘Centro Narcolessia’ (CN) of Bologna, located in the Emilia-Romagna Region in the north of Italy, is the only Italian centre offering a multidisciplinary management of narcolepsy (covering sleep, metabolic, psychological, and psychosocial aspects for both paediatric and adult patients), avoiding multiple referrals. The CN is the first Italian centre in terms of number of assisted patients, 71% of whom come from outside the Emilia-Romagna Region (the most distant one comes from Pantelleria, an island 1553 km far from the CN). Unmet patients’ needs at regional level force them to undertake long journeys to seek for consultations, with consequent delayed access to diagnosis and care and high direct and indirect disease-related costs, possibly worsening the control of disease symptoms and the prevention of drug side effects. Indeed, according to the Authors’ clinical practice experience, patients may refrain from scheduled outpatient visits due to high costs to reach the Sleep centre.

In this regard, Telemedicine (TM) is one of the most promising approaches. TM is the “practice of medicine using electronic communications, information technology, or other means between a licensee in one location and a patient in another location” [12]. The American Academy of Sleep Medicine supports TM as a means of advancing patient health by improving access to the expertise of qualified Sleep Medicine specialists [13]. TM includes Televisits (TVs) via videoconference, a synchronous live interactive TM visit, in which “patients and providers are separated by distance but interact in real-time utilizing videoconferencing as the core technology” [13].

Several studies about the impact and outcomes of Sleep TM investigated various TM applications (e.g., TVs, home sleep test devices or telemetric titration methods, etc.) for the diagnosis, monitoring, treatment, education and follow-up of obstructive sleep apnoea [14–17]. Despite the scarceness of randomized controlled trials (RCT), the available studies suggest the non inferiority of TM vs in-person care in terms of patient satisfaction, adherence to treatment, and symptomatic improvement [17]. Moreover, some studies confirm that TM has the potential to facilitate patient access to sleep consultations [18–21]. However, clinical and economic benefits of Sleep TV procedures is still uncertain [22], and its impact, with the exception of stroke, has been rarely explored in the neurology field [23]. In particular, the potential of this innovative approach for the diagnosis and management of narcolepsy is still unknown. Robust randomized trials are needed to understand the impact of Sleep TM on patient outcomes, and health-care system accessibility [17].

The TENAR (TElemedicine for NARcolepsy) project will assess for the first time Sleep TM procedures for children and adults with narcolepsy. In particular, the project will assess the feasibility, accuracy, efficacy and safety of TVs applied to the diagnostic process and the multidisciplinary care of narcolepsy. The TENAR project combines the patient-oriented outcomes research approach with the theoretical approach of “move the healthcare where it really needs” [24] through TM and mobile internet devices.

## Aims

TENAR is a two-part project aiming at: 1. assessing the accuracy of TV for the diagnosis of narcolepsy (*Tele-triage study*) in children and adults with suspected narcolepsy; and 2. demonstrating the non-inferiority for EDS control of the multidisciplinary management through TVs vs standard in-person outpatient follow-up visits, while monitoring patient-centred outcomes (*Tele-multidisciplinary care – TMC - study*). The TENAR project is endorsed by the Italian Narcolepsy and Hypersomnias association (AIN onlus, www.narcolessia.org).

## Methods/design

TENAR is a monocentric project designed by the CN (‘Centro Narcolessia’ - Narcolepsy Centre), part of IRCCS Istituto delle Scienze Neurologiche di Bologna, an academic hospital, in the city of Bologna, Italy. The coordination of the project, data collection, management, analysis, and interpretation of data, writing of the reports will be performed by the CN. All Authors will have access to the final dataset.

### Tele-triage study

#### Study design and outcomes

The Tele-triage study aims at assessing the diagnostic accuracy of a sleep medicine assessment through a TV of patients with suspected narcolepsy, by means of a cross-sectional design. The index text will be the diagnostic judgment after a TV by a sleep specialist according to three levels: “probable narcolepsy”, “possible narcolepsy” or “excluded narcolepsy”. The reference standard will be the final diagnosis (“confirmed narcolepsy” or “excluded narcolepsy”), established after a standard work-up for the diagnosis of narcolepsy and other sleep disorders with EDS complaint according to the International Classification of Sleep Disorders (ICSD-3) criteria [1] (i.e. symptoms and objective in laboratory assessment, eventually including cerebrospinal fluid orexin level measurement). A physician blinded to the initial diagnostic suspicion will establish the final diagnosis on the basis of patients records, including test results. The primary outcome is the diagnostic accuracy (sensitivity, specificity); the secondary outcome is the inter-observer agreement between sleep experts on diagnostic orientation (according to 3 levels: “probable narcolepsy”, “possible narcolepsy”, or “narcolepsy excluded”) after in-person or TV assessment respectively.

#### Participants, setting and procedures

Children (any age) and adults admitted to CN outpatient clinic of the IRCCS Istituto delle Scienze Neurologiche di Bologna, Italy, for suspected narcolepsy will be invited to participate. After informed consent procedure, participants will undergo a sleep assessment through in-person office visit first or TV first, by two independent sleep experts. Both the type of visit and the examiner will be assigned randomly. During TV, patients will use a tablet (in a dedicated CN room) and the sleep expert an in-office PC (in a different room). In case of children, a parent/caregiver will be present at both assessments. The sleep assessment for suspected narcolepsy consists of a reliable semi-structured interview on narcolepsy symptoms [25].

At the end of the assessment, each examiner will express his/her diagnostic orientation (“probable”, “possible” or “excluded” diagnosis of narcolepsy). In the following months, all participants will undergo the reference standard work-up according to clinical practice.

#### Sample size and statistical considerations

Two hundred and fifty patients are necessary to prove the desired sensitivity of 94% (CI lower limit) of TV, keeping CI lower limit of specificity at 73%, expecting 40% prevalence of narcolepsy at the CN outpatient clinic referral. Interobserver reliability will be calculated by kappa statistics, which is the ratio of the observed agreement beyond chance to the potential agreement, according to the formula proposed by Fleiss [26]. Kappa values will be interpreted according to conventional groups (0.0–0.20 = slight agreement, 0.21–0.40 = fair, 0.41–0.60 = moderate, 0.61–0.80 = substantial, 0.81–1.00 = almost perfect) [27].

### Tele-multidisciplinary care (TMC) study

#### Study design and outcomes

The TMC study is a 12-month, two-arm, parallel, open RCT aiming to demonstrate the non-inferiority for EDS control of the multidisciplinary care of narcolepsy through TVs versus standard in-person follow-up care (Fig. 1). Primary outcome is EDS control (according to the Epworth Sleepiness Scale, ESS [28]). Secondary outcomes are the following: other symptoms control, compliance with treatment, metabolic control, quality of life, feasibility, patient and family satisfaction with care, safety, and disease-related costs. Primary and secondary outcomes, and related measures and timepoints for data collection are summarized in Table 1.

**Fig. 1 Fig1:**
[figure not shown]
Flowchart of the randomized controlled trial

**Table 1 Tab1:** Primary and secondary outcomes, measures and timepoints

Outcomes	Measures	Timepoints (months)
Primary		
EDS	ESS (adults) [28] ESS-CHAD [32] (adolescents)	0, 3, 6, 9, 12 incident patients 0, 6, 12 prevalent patients
Secondary		
Other symptoms	Cataplexy diary, NSS [33], BDI [34], STAI [35] (adults) CDI2 [36], MASC [37] (adolescents) Global Impression Scale [38] (physicians)	0, 3, 6, 9, 12 incident patients 0, 6, 12 prevalent patients
Compliance to treatment	Clinical consultation	0, 3, 6, 9, 12 incident patients 0, 6, 12 prevalent patients
Weight	Standard weight scale provided to each patient	0, 3, 6, 9, 12 incident patients 0, 6, 12 prevalent patients
Lipidic/glycaemic control*	Laboratory tests	0, 12
Caloric intake	Food diary	0, 12 [0, 3, 6, 9, 12 patients with metabolic problems]
Physical activity	Short-IPAQ [29]	0, 12 [0, 3, 6, 9, 12 patients with metabolic problems]
Satisfaction index	CoTenar (patients and caregiver)**	6, 12
Quality of life	SF-36 (adults) [39] PedsQL [40] (adolescents)	0, 6, 12
Number (%) of full dropouts		At the time of censorship
Number (%) of partial dropouts (patients changing procedure)		At the time of arm change
Adverse drug reactions	Clinical consultation	0, 3, 6, 9, 12 incident patients 0, 6, 12 prevalent patients
Costs and accidents	Interview (patients and caregivers)	0, 6, 12
Other feasibility indexes	Failure system report (physicians and patients)	After each TV

*Glucose, insulin, HbA1c, triglycerides, total, LDL and HDL cholesterol, TSH, glycaemia, insulin, glycated haemoglobin, HDL, triglycerides, total, LDL, uricemia, TSH, FT4, FT3, complete blood count, AST, ALT, gamma-GT, alkaline phosphatase, creatinine. ** Adapted from CoSM-S [41]

#### Population, intervention and procedures

Adolescents (≥14 years old) and adults with a diagnosis of narcolepsy according to ICSD-3 [1] criteria soon after the diagnosis (“incident”) or with established diagnosis (“prevalent” subjects) in charge at the CN of the IRCCS Istituto delle Scienze Neurologiche di Bologna, Italy, and able to provide consent are eligible. Exclusion criteria are the following: major psychiatric disorders; inability to read, write, or using a tablet; and no Internet access.

Patients who provide informed consent will undergo the following baseline in-person assessment by different experts through standardized tools (see Table 1):
sleep assessment;endocrine/metabolic assessment, with measurement of weight, height, waist circumference, blood pressure, heart rate; anda counselling session on the psychosocial impact of narcolepsy.

Patients will also be requested to complete a physical activity questionnaire [29], and to provide a 24-h food diary. In addition, a blood sample will be collected for a metabolic (lipid and glucose profile, and thyroid function) evaluation.

After baseline procedures, patients will be consecutively randomly allocated in 1:1 ratio either to TMC via videoconference or to standard in-person follow-up in-office visits (control arm). The randomization list (stratified for three groups: children, adults with incident condition, adults with prevalent condition) and allocation will be generated by an automatic web-based system after inclusion.

The TMC will consist of scheduled TVs through a tablet and remote data collection through an ad hoc designed electronic case report form (e-CRF). A videoconference service will be used. The TV will be performed aiming at assessing the patient’s condition, and his/her need/response to treatments. TVs will end with therapeutic prescriptions according to usual practice, until the next follow-up TV. A formal report of the sleep assessment through TV will be sent by mail to the patient. The standard in-person follow-up care consists in scheduled (3–6-9 months) usual in-office visits, performing the same assessments, data collection and therapeutic prescriptions according to usual practice. The scheduling of follow-up TVs or in-person visits (at 3–6-9 months) will be based on the patient’s condition and needs (see Table 1).

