#### Sample size and statistical considerations

A total of 176 patients (88 per arm) are required to prove that the 95% lower limit of one-sided CI will be above the non-inferiority limit of − 1.5 ESS points difference (standard deviation of 4), with 80% of power. A previous RCT used a non-inferiority margin of 2 ESS points and 80% as minimal power to compare pitolisant versus modafinil in patients with narcolepsy [30]. As the TMC study will not test drugs, we decided to adopt a stricter margin (1.5 ESS points). The standard deviation value (±4) was based on the Italian validation study of ESS [28]. Considering 15% of dropouts, the sample was enlarged to 202 (101 per arm). Repeated measures ANOVA will be used to compare EDS between groups at baseline and after 1-yr of follow-up.

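### Minor: randomisation balances incident or prevalent status in adults but not in adolescents, leaving room for chance imbalance and a little lost precision

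*Protocol article*

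**What the plan says.** All references are to the protocol article, section Tele-multidisciplinary care (TMC) study.

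- **Eligibility** (Population, intervention and procedures): the trial admits "Adolescents (≥14 years old) and adults with a diagnosis of narcolepsy according to ICSD-3" criteria, either "soon after the diagnosis (“incident”) or with established diagnosis (“prevalent” subjects". Neither status is restricted by age.
- **Randomisation** (same subsection): patients are "consecutively randomly allocated in 1:1 ratio", from a list "stratified for three groups: children, adults with incident condition, adults with prevalent condition". Since nobody under 14 is eligible, the children stratum can only be the adolescents.
- **Schedule** (Table 1): the primary outcome is collected at "0, 3, 6, 9, 12 incident patients 0, 6, 12 prevalent patients". The same row names the adult and the adolescent version of the Epworth scale, so the rule applies at every age: four assessments after baseline for incident patients and two for prevalent patients.
- **Analysis** (Sample size and statistical considerations): repeated measures ANOVA of sleepiness at baseline and after one year. No adjustment for disease status is mentioned.

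**The concern.** The list separates incident from prevalent adults, and Table 1 uses the same distinction to set the density of follow-up for everyone. Within the adolescent stratum it is not controlled. A newly diagnosed 15-year-old and a 17-year-old under established care are interchangeable to the randomisation system, and the article gives no reason for treating the two age groups differently.

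If ESS moves more in the year after diagnosis than under established care, which is plausible but not stated, an arm that happens to receive more incident adolescents would show a somewhat different mean change. It would also have more scheduled visits per adolescent. Adjusting only for the three strata as defined would not recover this, because the missing split lies inside one of them. At stake is some precision in the primary comparison and the balance of a baseline factor that the design already controls in adults.

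**Working it through.** **1. The plan's own sample size.** Inputs: "95% lower limit of one-sided CI", so one-sided alpha 0.05; "non-inferiority limit of − 1.5 ESS points difference (standard deviation of 4), with 80% of power".

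n per arm = 2 × (1.645 + 0.842)² × 4² / 1.5² = 2 × 6.18 × 7.11 ≈ 88, or 176 in total. This reproduces the stated figure. The enlarged sample is 202, or 101 per arm.

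**2. Standard error of the primary comparison.** With SD 4 and 101 per arm: 4 × √(2/101) = 0.56 ESS points.

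**3. Chance imbalance among adolescents.** The article gives neither their number nor their incident share. Assume 40 adolescents, 20 per arm, 20 of them incident. With only the stratum total balanced, the number of incident adolescents in one arm is hypergeometric:

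- variance = 20 × 0.5 × 0.5 × (20/39) = 2.56, SD = 1.60 patients
- SD of the difference between arms = 2 × 1.60 = 3.20 patients
- SD of the difference in incident share = 3.20/20 = 0.160
- probability of a difference of 4 or more patients (20 percentage points) = 34%

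**4. Effect on the whole-trial result.** Let D be the difference in 12-month ESS change between incident and prevalent patients (assumed; the article gives none). SD of the chance component = 3.20 × D / 101:

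- D = 4: 0.13 ESS points
- D = 2: 0.06 ESS points

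**5. Range of assumptions.** Incident share 30% to 70%.

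| Adolescents (assumed) | SD of difference in incident patients | P(difference ≥ 4) | P(difference ≥ 6) | SD of ESS component, D = 2 | SD of ESS component, D = 4 |
|---|---|---|---|---|---|
| 20 | 2.10–2.29 | 14–18% | 1–2% | 0.04–0.05 | 0.08–0.09 |
| 40 | 2.94–3.20 | 30–34% | 8–11% | 0.06 | 0.12–0.13 |
| 60 | 3.58–3.91 | 40–44% | 16–20% | 0.07–0.08 | 0.14–0.15 |

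In 95% of allocations the difference stays within 4 to 8 incident adolescents, depending on the row. That shifts the arm difference by at most 4 × 2/101 = 0.08 to 8 × 4/101 = 0.32 ESS points.

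**6. Share of the variance.** At 40 adolescents and D = 4: 0.13² / 0.56² = 0.017/0.314, about 5% of the variance of the estimate. This share is already part of that variance, because differences between incident and prevalent patients belong to the between-patient spread.

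**The case against.** The strongest reply is that nothing here is wrong. Keeping a small age group as one stratum avoids sparse cells and incomplete blocks, and choosing three strata over four is a matter of judgement. Adolescents are still allocated 1:1, so the expected incident share is the same in both arms. Any gap is chance, and the confidence interval already allows for it. The primary comparison uses baseline and one year, which both schedules share, and status sets the schedule in the same way in both arms, so extra visits act only indirectly. The size rests on three inputs that the article does not give. Finally, covariates are commonly left to an analysis plan, which is not shown here.

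Most of this stands. It rules out two stronger readings that a reader might infer:

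- **That the list biases the trial, or produces a false difference between arms.** It does not. Visit mode is still assigned at random with respect to status.
- **That the adolescent result is badly compromised against the margin.** Within 40 adolescents the component at D = 4 has SD 0.160 × 4 = 0.64, and it is tempting to set this beside 1.5. But the article plans no adolescent estimate, and the margin applies to the whole trial. With 20 per arm the standard error would in any case be 4 × √(2/20) = 1.26, however the strata were drawn.

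What survives is narrower. The article states its strata in full and gives no reason for the uneven treatment. Status is known for every patient before randomisation, so using it costs nothing.

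**Conclusion.** The point holds as a minor one. Status is balanced by design in adults and left to chance in adolescents, while the same document lets status set visit density at all ages. The randomised comparison is valid, the required sample size is unchanged, and there is no systematic bias. The consequence is possible chance imbalance and a small loss of precision: an SD of about 0.13 ESS points overall, against a standard error of 0.56 and a margin of 1.5. That figure assumes 40 adolescents, half incident, and a 4-point difference in change by status, none of which is in the article. It falls to 0.06 at 2 points and runs from 0.04 to 0.15 over the range shown.

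**What to change.** In the primary analysis described under Sample size and statistical considerations, include incident or prevalent status, as recorded before randomisation, for all patients including adolescents, together with age group (adolescent or adult). In a repeated measures ANOVA of baseline and one year, each factor should enter with its interaction with time. A main effect alone would leave the comparison of change between arms untouched. State this before outcome data by arm are seen. If the full analysis plan already does so, nothing further is needed.

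If randomisation has not started, the adolescent stratum may optionally be split by status, giving four strata in the web-based system. The price is one small stratum that may end with an incomplete block. If randomisation has started, keep the list and rely on the adjustment.

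Cost: a few model terms based on data already held, with no extra patients or visits. The planned 176 evaluable and 202 enrolled patients stay as they are.
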